**Figure 3 fig3:**
[figure not shown]
CONSORT flow diagram for attrition.

Propensity scores, calculated via logistic regression, will ensure balanced covariate distribution between intervention and control groups, enhancing the validity and reliability of the randomized controlled study (Rosenbaum and Rubin, 1983). Participants will complete secure online questionnaires via Survey X-act, collecting sociodemographic data (age, gender, education) job-related factors (function, seniority, occupation, responsibility, functional area), and outcome data. Aggregated local baseline assessments (T0) will guide need analysis and curriculum adjustments, as recommended by reviewers of leadership training, to optimize learning and transfer (Lacerenza et al., 2017). Internal HR-trainers will be blinded to subsequent intervention data (T1, T2) to minimize training biases. Growth modeling procedures in leadership training have proven effective in evaluating leader changes during interventions (Day et al., 2021). SAS PROC MIXED (SAS Institute Inc, 2022) will be used to fit the Growth Model. An unconditional model will predict longitudinal data, followed by conditional linear growth models examining interaction effects (*p*-values) of person-level covariates on short-term (T0, T1) and long-term (T0, T2) trajectories for all primary outcome variables. Rasch analysis will calculate Cronbach’s Alpha (reliability), item fit, eigenvalues (dimensionality), and differential item function (DIF). Process evaluation data will be analyzed using the package “Markov chain” (Spedicato, 2017) for discrete time Markov chains, examining the progression of Kirkpatrick levels and relevant resilience factors implemented over time. Descriptive analysis will be performed using R (R Core Team, 2024) to show influencing factors on the leader resilience training and resilience processes. Participant data from Survey X-act will be managed by a designated research team member using unique participant codes and analyzed by an external statistician to reduce research biases. Data retention is set for 5 years post-study.

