### Research design

2.3

Consistent with recommendations from the latest comprehensive meta-review of resilience training in organizational contexts (Scheuch et al., 2021), this study is a randomized controlled trial (RCT) to examine the impact of behavioral resilience training in leader contexts. The majority of participants are recruited from the private organization, due to massive resource planning in the public organization. Following prior organizational resilience studies (Vanhove et al., 2016), we will assess primary outcomes to demonstrate resilience capacity (Britt et al., 2016) and evaluate dynamic resilience pathways over time (Masten and Reed, 2002), in this study through three measurements. Resilience in response to stressors of varying intensity is expected to show different outcome trajectories, allowing for more accurately observation and assessment in the context in which it occurs (Pangallo et al., 2015). To achieve this, participants will complete questionnaires at multiple time points: before (T0), during (T1), and after the intervention (T2). This longitudinal analysis will provide insights into resilience dynamics in leader settings and evaluate outcomes after the extended intervention, as suggested by several resilience researchers (Vanhove et al., 2016; Robertson et al., 2015; Ukhova, 2020). For secondary outcomes of interest, using a mixed-method design, we will assess training effects via the Kirkpatrick model (Kirkpatrick and Kirkpatrick, 2016), which also allows indirect analysis of the implemented resilience factors. Additionally, we will conduct a process evaluation of contextual conditions during and after the intervention (T1, T2) and explore participant experiences using various process evaluation frameworks proposed by intervention researchers (Moore et al., 2015; Randall et al., 2007; Braun and Clarke, 2006). The logical model for the framework variables and data sources used in the learning and development evaluation part of the study is mapped in Appendix 2. The overall aim is to evaluate the effects, processes and underlying mechanisms of the intervention, providing insights into what, why, and how of training psychological resilience in leader contexts. The total research design is outlined in Table 1 according to SPIRIT 2013 recommendations for standard protocols (Chan et al., 2013) showing different research and implementation activities.

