**Table 1 tab1:** The schedule of enrolment, interventions, and assessments.

Study period							
	Enrolment	Allocation	Baseline	Intervention (Part I)	During	Intervention (Part II)	Follow-up (< 3 months)
TIMEPOINT		0	T0		T1		T2
ENROLMENT							
Eligibility screen							
Informed consent							
Allocation							
INTERVENTIONS							
Resilience training intervention (20 sprints)							
No intervention (control group)							
ASSESSMENTS							
Socio/ demographic variables: age, gender, education, job function, seniority, occupation, responsibility, functional area							
Primary outcome variables: Perceived stress, CD-RISC 10, RAW, WEMWBS, Flourishing							
Secondary outcome variables: training evaluation (Kirkpatrick x 20)							
Secondary outcome variables: process evaluation (self-constructed scales)							

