### Randomization of participants

2.5

Following guidelines from a previous meta-review on resilience training in organizational contexts (Robertson et al., 2015), individual participants from organizational units will be randomly assigned to either the experimental or control group using computer-generated simple randomization. To mitigate contamination risks, the intervention group will from the beginning be advised not to share intervention content and training materials with the control group. HR-business partners will monitor the participating units, where leaders also work across the organization in many diverse team compositions, which we expect can reduce direct interaction, intervention conversations, and spill-over effects. Both groups will continue with their regular job responsibilities; however, the experimental group will also participate in weekly training sessions and additional self-directed training between sessions. The control group will only complete questionnaire measurements before, during, and after the intervention. After the final measurement, control group participants will be offered a condensed period of resilience training. This behavioral intervention study will be reported using an extension of the CONSORT Statement for social and psychological interventions (Montgomery et al., 2018).

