### Data management and statistical analysis of results

2.7

*A priori* power calculations were conducted using G*Power 3.1 (Faul et al., 2007) to determine the required sample size for a repeated measure and ANOVA assessing the interaction between time (three waves) and group (intervention versus control). The analysis for repeated measures, within-between interaction, was based on the following parameters: a medium Cohen’s effect size (*f* = 0.25), a significance (Alpha) level of 0.05, desired power of 0.08, and correlation among repeated measures of 0.5 for two groups and three measurements. The power analysis indicated that a total sample size of 28 participants (14 per group) was deemed necessary to achieve 80% power to detect a group x time interaction in this multi-wave organizational trial. Potential attrition across waves is accounted for as indicated in the CONSORT 2010 Flow Diagram in Figure 3, illustrating sample size planning for 30% attrition, assuming attrition occurs evenly from recruitment and across the waves with a rate of approximately 10% throughout the study. However, the aim is to increase the final target sample size to approximately 100 participants to enhance the validity of the study, due to pressures from extreme times in the organizations.

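### Propensity scores cannot ensure covariate balance in a randomised trial; if used for weighting at 28 to 40 participants they would probably cost precision, so adjust directly for baseline and organisation

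*Protocol article*

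**What the plan says.** Section 2.5 (Randomization of participants) says that individual leaders "will be randomly assigned to either the experimental or control group using computer-generated simple randomization". It mentions no blocking, stratification or minimisation. Section 2.3 adds: "The majority of participants are recruited from the private organization".

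Section 2.7, in the text after Figure 3, then says: "Propensity scores, calculated via logistic regression, will ensure balanced covariate distribution between intervention and control groups". It credits this step with improving the validity and reliability of the randomised study. It names neither the covariates in the score nor its use (balance check, covariate, weighting or matching). Table 1 lists the background variables collected: "age, gender, education, job function, seniority, occupation, responsibility, functional area".

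On size, section 2.7 says that "a total sample size of 28 participants (14 per group) was deemed necessary to achieve 80% power", plans for 30% attrition, and then says that "the aim is to increase the final target sample size to approximately 100 participants".

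The effect analysis is a growth model fitted in a mixed-model procedure, covering T0 to T1 and T0 to T2.

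**The concern.** Propensity scores are made for studies in which the chance of treatment depends on unknown features of the participant. Here the trial sets that chance itself. The 14 per group in the power calculation implies 1:1, so the true score is 0.5 for everyone. A logistic model of arm on covariates can then pick up only the accidental differences of this one allocation.

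Two things are at stake. First, the article gives an assurance that the method cannot deliver. Second, with few participants per fitted parameter, the scores spread widely around 0.5, and weighting by them can lose more precision than the improved balance returns. Leaving the covariates and the use of the score open also adds analyst choice to a comparison that randomisation has already made unbiased.

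**Working it through.** **Inputs from the protocol article.** f = 0.25, alpha 0.05, correlation 0.5, two groups, three waves, total 28 (14 per group), 30% attrition, target about 100 (section 2.7); eight background variables (Table 1); simple randomisation (section 2.5).

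**1. The plan's own figure.** For the within-between interaction, λ = f² × N × m / (1 − ρ), with df1 = (2 − 1)(3 − 1) = 2 and df2 = (N − 2)(3 − 1). At N = 28, λ = 0.0625 × 28 × 3 / 0.5 = 10.5, df2 = 52, power 0.812. At N = 26, power is 0.778. So 28 is reproduced for 80% power (the 0.08 printed for desired power is a slip). Allowing for attrition, 28 / (1 − 0.30) = 40. The sizes to examine are therefore 28, 40 and 100.

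**2. Participants per fitted parameter**, if all eight variables enter with one parameter each: 14/8 = 1.75 per arm at N = 28, 20/8 = 2.5 at N = 40, 50/8 = 6.25 at N = 100.

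**3. What a fitted score does under true 1:1 simple randomisation.** This was simulated with eight independent normal covariates, a logistic fit, inverse-probability weights, and one follow-up score correlated 0.5 with baseline. The variance ratio is the variance of the weighted effect divided by that of the plain difference in means. Ranges are across separate simulation runs.

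| N | Apparent AUC (true 0.50) | Mean absolute standardised difference, before → after weighting | Variance ratio, covariates not prognostic | Variance ratio, covariates explain 30% of variance |
|---|---|---|---|---|
| 28 | 0.81–0.82 | 0.31 → 0.15 | 1.45–1.57 | 1.29 |
| 40 | 0.76 | 0.26 → 0.10 | 1.43–1.47 | 1.11 |
| 100 | 0.66 | 0.16 → 0.02 | 1.11–1.15 | 0.76–0.81 |

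Weighting reduces imbalance at every size, but at 28 it leaves about half of it (0.15/0.31). The balance is not ensured, and at 28 to 40 precision is lost in both scenarios.

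Entering the score as a covariate instead gives ratios of about 1.5, 1.3 and 1.1 without prognostic value, and 1.15, 0.95 and 0.79 with 30% explained.

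If the categorical variables were dummy coded to 17 parameters (an assumption), the fit would separate or fail in 96% of trials at N = 28, 40% at N = 40 and practically none at N = 100.

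**4. Baseline adjustment, for comparison.** At ρ = 0.5, a T0-to-T2 change contrast has variance 2(1 − 0.5) = 1.0 relative to an unadjusted follow-up comparison. Adjustment for the baseline score gives 1 − 0.5² = 0.75. The simulation gave 0.76 to 0.82 at 28, 40 and 100.

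**5. Allocation.** Simple randomisation of 28 gives exactly 14/14 with probability 0.149, and 18/10 or worse with probability 0.185. For an 18/10 split, λ is multiplied by 4 × 18 × 10 / 28² = 0.918, giving 9.64 and power 0.78 against 0.81.

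With blocks stratified by organisation and one further factor (assumed 80:20 organisation split), the mean organisation imbalance at N = 28 falls from 12 to 6 percentage points and the mean arm-size difference from 4.1 to 1.4. Factors not stratified on stay at 15 points.

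**The case against.** The strongest reply is that the model examined here is partly assumed. The article names no covariates, does not say that all eight enter, and mentions neither weighting nor matching. Such detail may sit in an analysis plan that is not shown. This stands, and it makes the variance figures conditional. It does not rescue the claim of ensured balance, which no choice of covariates or use can make true.

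Four stronger readings are tempting, and the document does not support them.

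- **That the scores merely fit noise, to the trial's harm, at every size from 28 to 100.** At the stated target with eight parameters the loss is 11 to 15% without prognostic covariates. There is a gain if they explain 30% of outcome variance. Apparent AUC by itself shows neither bias nor lost precision.
- **That the analysis leaves out the baseline outcome.** T0 is already a response in the growth model. What the article does not state is adjustment for it.
- **That better allocation would give covariate balance for free.** It would secure arm size and organisation only. Even minimisation on all eight factors (assumed binary) leaves some factor more than 20 points apart in 77% of trials at N = 28. Table 1 also places allocation before T0, so questionnaire covariates are not yet available then.
- **That simple randomisation is a flaw in itself, or that the public organisation is small.** Simple randomisation is valid and unbiased, and unequal arms cost little power. The Method section calls both organisations large; only the majority share of private participants is stated.

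**Conclusion.** The concern holds in a limited form. The claim that propensity scores ensure balance, and so strengthen validity, is wrong as written whatever the analysis plan adds. The practical harm depends on use and size. If eight variables enter and the score is used for weighting, variance rises by about 45% or somewhat more at 28 to 40 participants without prognostic covariates, and by about 10 to 30% if they explain 30% of outcome variance. At about 100 the effect is small and may be favourable. The cost is efficiency, analyst discretion and a false assurance, not bias.

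These sizes rest on assumptions not in the article: all eight variables in the score, one parameter each, independent normal covariates, prognostic strength between 0 and 30%, and a single follow-up comparison standing in for the mixed model.

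**What to change.** Delete the propensity-score step and the sentence that claims balance from it. Prespecify direct covariate adjustment in the mixed model for organisation and for the baseline value of each outcome. Choose one way of using T0 and state it: either T0 as a covariate with T1 and T2 as responses, or T0 kept as a response with baseline means constrained equal across arms. Do not do both, since that would use T0 twice.

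If allocation has not yet taken place, generate it in one batch after recruitment closes, 1:1 by permutation within organisation. Late sign-up is already an exclusion criterion and organisation is known without a questionnaire, so this looks feasible. It secures arm size and organisation balance only, and the power gain from equal arms is small (0.78 to 0.81 for 18/10 against 14/14 at N = 28). If allocation is done, make the analysis change alone.

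The cost is revised analysis wording and, where still possible, a different random list. No extra data or participants are needed.

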**Figure 1 fig1:**
[figure not shown]
Main components of the foundational leader resilience model, adapted with permission from Britt et al. (2016).

The resilience study aims to equip leaders with various resilience opportunities in two large organizations (private and public) headquartered in Denmark. The operational objective of the study involves designing, implementing, and conducting the contextualized and comprehensive leader resilience training intervention that adopts a multidisciplinary, multimodal, and multilevel supportive approach. The study contributes with empirical knowledge on collective resilience training in leader contexts for leaders leading themselves and others and pinpoints implications for future empirical resilience interventions.

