### Implementation of the leader resilience training program

2.2

The comprehensive framework for leader training includes a curriculum with 18 subcategories derived from the three multidisciplinary core components, covering a wide range of adaptation opportunities. The program is divided into two parts: Part I includes 18 basic training sessions, and Part II comprises 18 advanced sessions, totaling 36 pre-designed training sessions. This division ensures a progressive approach and macro program flexibility, as demonstrated in previous studies (Ungar and Jefferies, 2021; Las Hayas et al., 2019). To tailor the curriculum to the specific needs of participant organizations, a co-creation process will be employed. This involves collaboration with participant organizations to align the training program with their local visions and resilience needs. The selection of the final curriculum will be based on local aggregated baseline assessment data and will follow specific workshop protocols. The contextualized curricula will consist of 20 weekly one-hour resilience training sessions (embedded in weekly resilience-sprints), with 10 sessions in each part (Part I and Part II). Recognizing that resilience development requires time and effort, the program is designed as a prolonged training intervention, emphasizing reflection and experiential engagement in fostering resilience (Masten, 2011; Elkington and Breen, 2015; Cooper et al., 2013).

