#### Qualifying the measurements tools

2.6.1

To ensure contextual relevance, all outcome measurements, curricula, materials, and activities will be aligned with corporate language requirements, utilizing original and translated validated questionnaires for both Danish and English-speaking organizations. One necessary questionnaire will be translated into Danish following the forward-and back-translation guidelines (Beaton et al., 2007). Further, we will employ the Rasch methodology (Rasch, 1960) to assess the psychometric properties of the questionnaires. Recognized in Business and Management Studies for handling subjective, ordinal, and non-observable variables (García-Pérez and Yanes-Estévez, 2022), the Rasch model allows for constructing a unidimensional scale based on participants’ evaluations and testing the fit of the sample data to this model (Stemler and Naples, 2021). Using the software package RUMM2030 (Andrich et al., 2009), we will specifically use the Polytomous Rasch model that examines the likelihood of individual leaders providing endorsement responses to each test item, considering unequal difficulty levels of endorsement across test items (Boone et al., 2014).

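### Organisation sets the curriculum, trainers and language but has no stated place in the outcome models; the cost is modest precision and an unclear pooled effect, not bias

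*Protocol article*

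**What the plan says.** The Method section places the study "in two large organizations (private and public) headquartered in Denmark". Section 2.3 adds: "The majority of participants are recruited from the private organization, due to massive resource planning in the public organization".

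Several features are fixed at organisation level:
- **Curriculum.** Section 2.2: "The selection of the final curriculum will be based on local aggregated baseline assessment data". Both versions draw on one bank "totaling 36 pre-designed training sessions" and share one format: "The contextualized curricula will consist of 20 weekly one-hour resilience training sessions".
- **Trainers.** Section 2.2 has internal HR staff of each organisation deliver the sessions.
- **Language.** Section 2.6.1 aligns questionnaires and materials with the corporate language, "for both Danish and English-speaking organizations".

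Section 2.5 allocates individual leaders by simple computer-generated randomisation and states no stratification.

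Table 1 and section 2.7 list the background variables: age, gender, education and "job-related factors (function, seniority, occupation, responsibility, functional area". Section 2.7 then describes an unconditional growth model, followed by conditional models that examine interactions of person-level covariates with the T0-T1 and T0-T2 trajectories of all five primary outcomes. Neither the lists nor the model description names organisation.

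**The concern.** The version of the training that a leader receives, the people who deliver it and the surroundings in which stress is reported all depend on the organisation. Section 2.3 itself describes a circumstance peculiar to the public organisation, heavy enough to limit recruitment there. Perceived stress is a primary outcome, so different trends over time in the two organisations are plausible, though the article does not report any.

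Two things are at stake. First, without an organisation term, a difference in trend that is common to both arms of an organisation is left in the residual, and precision is lost on every primary outcome. Second, the single pooled effect is an average over two tailored versions, weighted to the organisation that supplies most leaders, and nothing in the stated analysis shows how each contributed.

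**Working it through.** **The plan's own figure.** Section 2.7 gives N = 28 for a group x time interaction with f = 0.25, alpha 0.05, correlation 0.5, two groups and three waves. With lambda = f² x N x m / (1 - rho) = 0.0625 x 28 x 3 / 0.5 = 10.5, df1 = 2 and df2 = (28 - 2) x 2 = 52, power is 0.812; at N = 26 it is 0.778. So 28 is reproduced for 80% power. (The 0.08 printed in that section is a separate slip.)

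**Inputs not in the document.** Public share p: assumed 0.2 to 0.4. Difference in trend between organisations d: assumed 0.5 to 1.0, in SDs of change. Residual variance of change is set to 1 and the arms are taken as equal.

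**Formulas.** The omitted trend adds v = p(1 - p)d² to the variance of change. The variance of the arm difference goes from 4/N to 4(1 + v)/N, so the SE is multiplied by sqrt(1 + v).

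| p | d | v | Share of change variance, v/(1+v) | SE factor | SE at N = 28 (0.378 if adjusted) | SE at N = 100 (0.200 if adjusted) |
|---|---|---|---|---|---|---|
| 0.2 | 0.5 | 0.04 | 3.8% | 1.020 | 0.385 | 0.204 |
| 0.4 | 0.5 | 0.06 | 5.7% | 1.030 | 0.389 | 0.206 |
| 0.2 | 1.0 | 0.16 | 13.8% | 1.077 | 0.407 | 0.215 |
| 0.4 | 1.0 | 0.24 | 19.4% | 1.114 | 0.421 | 0.223 |

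**One loss, not two.** The error that chance imbalance in organisation puts into the arm difference has SD d x sqrt(4p(1 - p)/N) = sqrt(4v/N). That is 0.076-0.185 at N = 28 and 0.040-0.098 at N = 100. It is exactly the added term above and combines in quadrature: 0.378² + 0.076² = 0.385². It must not be added to the variance share as a second cost.

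**Power on the plan's inputs.** Dividing lambda by 1 + v, as an approximation, gives at N = 28 a power of 0.795 (p 0.2, d 0.5), 0.747 (p 0.2, d 1.0) and, as an outer limit, 0.713 (p 0.5, d 1.0). The N needed for 80% becomes 30, 32 and 34. With organisation x time in the model, power is 0.811 and N stays 28. At N = 100 power exceeds 0.999 either way.

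**Simulation** (4,000 trials per setting, p = 0.2, change scores, equal arms). Without an organisation term, type I error was 0.044 to 0.055 and the mean estimate was unbiased. At N = 100 with an assumed effect of 0.5 SD of change, power without and with the term was 0.673 and 0.690 (d 0.5), and 0.640 and 0.688 (d 1.0).

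**Interpretation.** Suppose, for illustration, that the effect is 0.5 SD in the private organisation and 0 in the public one. At p = 0.2 the pooled effect is 0.8 x 0.5 = 0.40. Simulation gave 0.399 without and 0.402 with the organisation term, so the term restores precision but does not reveal the difference; only estimates by organisation do. Those are imprecise: the SE of the organisation x group contrast is 1/sqrt(p(1 - p)) times that of the main effect, which is 2.5 at p = 0.2 and 2.0 at p = 0.4.

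**The case against.** The strongest reply is that this rests on silence in a condensed article. The variable list in section 2.7 describes what the questionnaires collect, not the model terms, and the propensity-score covariates are not listed at all. Person-level may simply mean not occasion-level; trial arm is itself person-level, and so can organisation membership be. This stands in part. A reader might infer that the models exclude organisation, but the document does not say so. What can be said is that the article describes the model in some detail and, as described, gives organisation no place.

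The second reply also stands: both inputs to the size are assumed, and the upper end needs a large public share together with a 1 SD difference in trend.

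Third, a reader might infer that two different programmes are being read as one. The document does not support that. Both versions come from the same 36 sessions and three components, in the same 20-session format, and local tailoring is an intended part of the intervention. How far the two selections overlap is not stated.

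Fourth, organisational and external conditions are collected in the process evaluation (section 2.6.3.2). That helps explain results, but section 2.7 summarises influencing factors descriptively and does not use them to adjust the arm comparison.

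Finally, estimates by organisation will settle little. With N = 28 and 20% public there are about six public leaders, roughly three per arm. This is correct, and is why those estimates should be descriptive.

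**Conclusion.** The point holds as one of efficiency and clarity. The curriculum, trainers and language are set by organisation, allocation is not stated to be stratified by it, and the model as described omits it. If 20-40% of leaders are public and trends differ by 0.5-1.0 SD of change, the SE of the arm difference is about 2-11% larger than necessary. At N = 28 the lower end already takes power just under the planned 80%; at the target of about 100 leaders the loss is immaterial on the plan's own effect size.

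A reader might infer that the omission biases the trial or inflates false positives. It does not: individual randomisation keeps the estimate unbiased and type I error near 5%. A reader might also infer that the article claims its result for both sectors separately. It makes no such claim; its hypothesis concerns leaders, and it says openly that most are private. What remains is that the pooled effect is a weighted average of two tailored versions, and the stated analysis does not show this.

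**What to change.** 1. Carry an organisation identifier into the analysis data. It should already be known, since baseline data are aggregated locally to select each curriculum.
2. Include organisation and organisation x time as fixed effects in the model for each of the five primary outcomes. Two organisations are too few for a random effect.
3. Report the training-minus-control difference with its confidence interval for each organisation, labelled descriptive, without a formal claim about whether the organisations differ.
4. State that the pooled estimate refers to the curricula actually delivered, and give the share of leaders from each organisation.

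The cost is two degrees of freedom with linear time, or three with time as three categories (one for organisation, two for organisation x time), plus one extra table. No new data are needed.
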